### Outcomes

#### Acceptability and feasibility (phase 1).

The main aim of phase 1 is to assess the feasibility and acceptability of various aspects of the study setup. Regarding feasibility, phase 1 will provide insights into the best way to integrate the various study components (the back pain simulator, the tasks and the measurement techniques) to identify changes in movement execution related to back pain. The results of the interview will provide information of the acceptability of the back pain simulator, the movement tasks, and the sensor technologies.

#### Pain (phase 2).

Perceived pain severity during task execution will be assessed via a VAS after completion of each movement task. Participants will rate pain intensity (0 = *no*
*pain*; 10 = *extreme*
*pain*), impairment due to pain (0 = *no*
*impairment*; 10 = *total*
*impairment*), and emotional distress due to pain (0 = *no*
*emotional*
*distress*; 10 = *extreme*
*emotional*
*distress*). The three pain ratings will be completed in both conditions after each task, resulting in 12 ratings each.

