### Study design

The study design is reported in line with the SPIRIT guidelines [44]. The experiment will take place in the EmpkinS laboratory in Erlangen, Germany. A repeated measures design will be used. Pain-free participants will execute standardized movement tasks with a mechanical low back-pain simulator (PainSim+) and without (PainSim-) a mechanical back-pain induction. An a priori computer-generated list based on random numbers created by one experimenter will be used to randomize the order of the conditions within each subject. S1 Fig provides an overview of the procedure of both phases.

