### Eligibility Criteria

Participants are eligible for inclusion if they meet the following criteria:

1) Age between 18 and 65 years2) Sufficient knowledge of German (native speaker or C2 level)3) Body mass index (BMI) between ≥ 18 and ≤ 25 (due to the limited size range of the back pain simulator and Xsens suit, see below)4) Body height ≥ 155 cm (setup requirement for back pain simulator and Xsens suit)5) Good physical and mental health state (see exclusion criteria)

Exclusion criteria for participation are as follows:

1) Chronic back pain2) Depression (exceed cut-off score for clinically relevant depression symptoms of 22 on the General Depression Scale (German: Allgemeine Depressionsskala; ADS-L; [45])3) Serious diseases or conditions concerning the nervous system (e.g., severe epilepsy), musculoskeletal system (e.g., rheumatic arthritis), skin (e.g., acute neurodermatitis), and cardiopulmonary system (e.g., myocardial infarction); cancer, strokes; serious psychological disorders will be screened via the Web Screening Questionnaire for Common Mental Disorders (WSQ; [46])4) Acute infectious diseases (e.g., HIV/AIDS)5) Current pregnancy6) Acute herniation (e.g., spinal disc herniation)7) Acute back pain (ranging on a scale from 0 = *no pain* to 10 = *worst imaginable pain* between ≥ 5 and ≤ 10)8) Acute muscle and/or skeletal pain interfering with daily activities9) Diseases of the nerve roots and spine injuries10) Osteoporosis of the spine or back11) Surgery on or near the spine12) Diabetes mellitus (back pain simulator requirement, inter alia because of associated skin and soft tissue changes and higher risk of skin infections; e.g., [47])

We will follow an adaptive design and may change eligibility criteria for phase 2 based on the phase 1 findings.

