### Lab appointment

Prior to the lab appointment participants will be informed via e-mail about the following instructions and restrictions: Waking up at least three hours before the appointment, no eating and caffein consumption one hour before the appointment, no smoking or exercise two hours before the appointment, and wearing comfortable clothes with thin fabric (no dresses or skirts). The lab appointment begins with the experimenters obtaining written informed consent. Participants then provide a baseline saliva sample for stress assessment (s0), which includes carefully moving a cotton roll (Salivette®, Sarstedt, Nümbrecht, Germany) in their mouth for 1.5 min. Afterwards, their body weight, height, and waist and hip circumference are measured. Female participants additionally provide a saliva sample of 5 ml via passive drooling (pooling saliva in the mouth and allowing it to drip into the sample tube) for the analysis of progesterone and estradiol levels as they might influence pain perception [57,58] and stress responses [35,59]. The core part of the experiment is conducted under two conditions in randomized order, namely, once with and once without the back pain simulator to allow for within-subject comparison. Before each condition, participants complete the Short Stress State questionnaire (SSSQ-G; [60]) and provide another saliva sample (s1). Participants then perform six movement tasks: five from the Back Performance Scale [61] and a sit-to-stand task (comparable to [62]; adjusted arm position: hands are placed relaxed on the legs). Movement quality is rated by an experimenter (see Additional File 1), and a video of the movement execution is recorded. Throughout the tasks, participants wear an inertial measurement unit (IMU)-based motion capture suit (Xsens MVN, Movella, Henderson USA; for more details see [63]). In phase 2, this will be supplemented by the EmpkinS holographic 6D wireless locating technique and integrated localizable electromyography radio transponders (EmpkinS sensor technology; [64,65]). After each task, participants rate pain intensity, emotional distress, and pain-related impairment on a visual analogue scale (VAS). Following task completion, the SSSQ-G and a third saliva sample (s2) are collected. The entire procedure is repeated under the alternate condition (with/ without low back pain simulator), including an SSSQ-G assessment before and after the six movement tasks, as well as another saliva sample (s3) after the movement tasks. In total, each participant completes 2x6 movement tasks, provides 4 saliva samples, and 2x2 SSSQ-G assessments.

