### Experimental procedure

#### Movement tasks (Back Performance Scale and Sit to Stand Task).

The Back Performance Scale (BPS) was developed to measure performance of mobility-related activity in back pain [61]. It comprises five tasks: the sock test, roll-up test, finger-floor, distance test, pick-up test, and lifting test (see Additional File 1). Performance regarding the participant’s effort and execution of the tasks is assessed by using a 4-point ordinal scale from 0 (best performance, e.g., “Can do the task with ease in varied ways”) to 3 (worst performance, e.g., “Cannot perform the task at all or need external support”) with individual wordings for scoring categories for each movement task [61]. In the lifting task, an additional specification is to put a time limit of one minute and count the repetitions of the participant. To ensure proper execution and not ambition, participants are not informed about this time limit beforehand. The whole BPS sum score ranges from 0 to 15 with lower scores indicating better performance and back mobility.

The sit-to-stand task (STST) was originally developed to measure performance of lower extremity muscles [66] and has also been used in the context of CBLBP [67]. The task comprises standing up from a chair and sitting down again, which will be repeated three times. For the current study, the performance rating was adapted to match the rating scale of the BPS, i.e., performance of mobility-related activity is rated from 0 to 3 (see Additional File 1).

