#### Stress (phase 2).

Task-related stress is assessed via self-report before and after each set of movement tasks. For this purpose the SSSQ-G [60] will be used, a 24-item questionnaire answered on a 5-point Likert scale (1 = *not*
*at*
*all*; 5 = *extremely*). As a pre- and a post-version exist, the questionnaire allows for evaluation of changes in acute task-related stress. The SSSQ-G assesses six facets of subjective task-related stress: Distress, Worry, Confidence, Negative Affect, Motivation, and Self-evaluation. Higher scores indicate a higher subjective level of stress.

Psychophysiological stress markers include unstimulated saliva samples (Salivette®, Sarstedt, Nümbrecht, Germany) to measure salivary cortisol and alpha-amylase levels indicating HPA axis and sympathetic nervous system (re-)activity, respectively. Salivary samples will be collected at four timepoints: baseline (s0), before the first set of movements tasks (s1), directly after the two sets of movements tasks (s2), and 15 min after s2 (s3). Saliva samples will be analyzed in the laboratory of the Chair of Health Psychology at Friedrich-Alexander-Universität Erlangen-Nürnberg (Nürnberg, Germany). After the collection, samples will be stored at −20°C for a maximum duration of 12 months. If longer storage times will be necessary, samples will be stored at −80°C. A maximum of two freeze-thaw cycles will be permitted. Prior to analyzing cortisol and alpha-amylase concentrations, samples will be thawed and centrifuged at 2000g for 10 min. To determine cortisol concentrations Cortisol Saliva Luminescence Immunoassays (CLIA, IBL, Germany) and for alpha-amylase concentrations kinetic/ colorimetric enzymatic assays will be used. To account for influences of menstrual cycle hormones, progesterone and estradiol concentrations derived from unstimulated passive drool samples will be analyzed using either high-sensitive Enzyme-linked Immunosorbent Assays (ELISA) or Liquid Chromatography-mass Spectrometry (LC-MS), depending on expected concentration ranges and availability of sensitive assay kits.

We will further record a 1-channel electrocardiogram (ECG) with a wearable ECG sensor (Portabiles GmbH, Erlangen, Germany; Lead I according to Einthoven’s Triangle) during the movement tasks. From the ECG, we will extract heart rate (HR) and established heart rate variability (HRV) metrics as markers for autonomic (re)activity [75].

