### Statistical methods

Qualitative analysis on feasibility and acceptability in phase 1 will be carried out with MAXQDA Analytics Pro [80]. Data of phase 2 will be analyzed using a repeated-measures design. Correlations of dependent variables will determine if multivariate analyses of variance (MANOVAs) or separate analyses of variance (ANOVAs) are indicated, following common recommendations of moderate intercorrelation [81].

The first MANOVA will include the within-subjects factor *condition* (PainSim + vs. PainSim-) and dependent variables measuring task-related fear of movement, pain intensity, impairment and emotional distress. A second MANOVA will assess *mobility* (LROM, LF, MV). And a third MANOVA will examine stress (HRV, salivary cortisol, salivary amylase, subjective stress) in the same manner. Psychophysiological data (e.g., HRV-data) that deviate (significantly) from the other data (i.e., outliers) will be excluded in accordance with the established practices in the literature. The pattern of missing data is tested with MCAR-test. If the missing data is missing completely at random, we will conduct multiple imputation.

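### Order of conditions is randomised, but the phase 2 models name condition alone, so any period effect stays in the error term; a resting pain rating before each condition is an optional extra

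*Protocol article*

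**What the plan says.** - **Order.** Study design sets out a repeated measures design in which a computer-generated list "will be used to randomize the order of the conditions within each subject". It does not say whether the list is balanced or blocked.
- **Session.** Under Lab appointment, participants do six tasks, and then "The entire procedure is repeated under the alternate condition (with/ without low back pain simulator"), which makes 2 x 6 tasks.
- **Models.** Statistical methods says "The first MANOVA will include the within-subjects factor *condition* (PainSim + vs. PainSim"-), with fear of movement, pain intensity, impairment and emotional distress as outcomes. The mobility and stress models follow the same structure. No order, period or sequence term is named.
- **Pain ratings.** Lab appointment: "After each task, participants rate pain intensity, emotional distress, and pain-related impairment on a visual analogue scale (VAS"). Pain (phase 2): "The three pain ratings will be completed in both conditions after each task, resulting in 12 ratings each". Six tasks in two conditions account for all 12 ratings per scale. Before each condition only the stress questionnaire and a saliva sample are listed, and the VAS given before a task measures fear.
- **Pain at entry.** Eligibility Criteria excludes "Acute back pain (ranging on a scale from 0 = *no pain* to 10 = *worst imaginable pain* between ≥ 5 and ≤ 10"), so milder pain can enter. This item belongs to the online screening, not to the lab day.
- **Sample size.** d = .40, alpha = .05 and power .80 give N = 51, raised to 56 for dropout and missing data.

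**The concern.** In a two-period design, the second set of tasks can differ from the first for reasons unrelated to the simulator: participants know the tasks, or they are tired. Randomising order stops this from favouring one condition in expectation. It does not remove it from the data. If PainSim+ comes first, the period effect enters the within-person difference with one sign; if it comes second, with the other. A model with condition alone treats that systematic spread as noise. If chance puts more participants in one order, part of the period effect also lands in the estimate. At stake is some power and some precision in all condition models, from information that the trial already holds.

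The second, smaller matter is that no described pain rating is taken at rest. Whether simulator pain has gone once the device is off can then be judged only from ratings that also contain task pain, and only in participants who had PainSim+ first.

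**Working it through.** **1. The plan's own figure.** Paired t-test, two-sided alpha .05 (the article does not state sidedness), dz = .40. Noncentrality is .40 x √51 = 2.857 on 50 df, and power is 0.7999. N = 51 therefore reproduces to rounding (52 is the first N strictly above .80). At N = 56 power is 0.837.

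**2. Model for the difference scores.** Write D = T + p·s + e. D is PainSim+ minus PainSim-, s is +1 or -1 by order, e has SD 1, and p is the period effect in SDs of the difference scores within an order. The article gives no value for p; 0.25 and 0.50 are assumptions.

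**3. Order omitted.** With unrestricted randomisation, Var(D) = 1 + p², so the effective dz is .40 / √(1 + p²).
- p = 0.25: .40 / √1.0625 = 0.388.
- p = 0.50: .40 / √1.25 = 0.358.

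**4. Order and order-by-condition included.** The residual SD returns to 1 and the error df falls by one (50 to 49 at N = 51). Power is 0.800 at N = 51 and 0.836 at N = 56 with an even split, and about 0.79 and 0.83 with unrestricted randomisation.

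| N | p | Order omitted | Order included |
|---|---|---|---|
| 51 | 0.25 | 78% | 79-80% |
| 51 | 0.50 | 71% (73% if split near-evenly) | 79-80% |
| 56 | 0.25 | 81-82% | 83-84% |
| 56 | 0.50 | 75-77% | 83-84% |

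Simulation agrees with the formulae. The ranges run from unrestricted randomisation to an even split.

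**5. Shift from imbalance.** With n1 and n2 participants in the two orders, the condition-only estimate moves by p(n1 - n2)/N. For an illustrative 30 v 21 split and p = 0.50 this is 0.50 x 9/51 = 0.088 SD, against a planned effect of 0.40. Averaging the two orders with equal weight removes it.

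**6. What each term holds.** Let the period effect be π (second minus first), the carryover into PainSim- be L and the carryover into PainSim+ be L'. The mean of D is T - π - L with PainSim+ first and T + π + L' with PainSim- first. The order-by-condition term is the difference between these, so it mixes period and carryover. The order main effect reflects L - L'. The interaction is the term that takes the period effect out of the error of the condition contrast; the order main effect alone would not.

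**7. Residual pain.** With equal halves and L' = 0, the mean contrast is the average of T - L and T, which is T - L/2. One point of residual pain lowers it by 0.5 point, and an order term does not undo this. L cannot be estimated from the documents.

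**8. What resting ratings could show** (1:1 split assumed).
- As described, comparing PainSim- scores between orders (28 v 28) has 31% power at d = .40, and it confounds carryover with period.
- Comparing a resting rating before the second condition, adjusted for the first resting rating, gives 34%, 40% or 54% for assumed correlations of .3, .5 or .7. This is still a weak test.
- Descriptively, 0 of 28 with residual pain after PainSim+ would give an exact 95% upper limit of 1 - .025^(1/28) = 12.3%.

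**The case against.** Randomisation already protects the condition contrast from period effects in expectation, so leaving order out is not a bias of the design. That stands, and what remains is precision and chance imbalance. The loss also rests on assumed period effects, and at 0.25 SD it is only about two points. That stands too. Naming condition does not rule out order, and a separate analysis plan may add it. The answer is that the article does set out the model's factor, and the addition costs almost nothing.

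On pain, hypothesis 1 concerns task-related ratings, for which ratings after each task are the right measure. A resting rating answers a different question, and asking about back pain before each set may prime the fear ratings used for hypothesis 2. Asking in both conditions does not fully cancel this, because the second question follows simulator pain in only one order. These objections hold, and they are why the resting rating is optional.

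A reader might infer that, with no washout described, residual pain undermines the comparison. The documents do not support that. An article commonly leaves rest intervals to the full protocol, the timeline figure and session checklist are not shown, and the Procedure section says pain is assessed throughout the session. The absence of a described washout is therefore not a finding. Residual pain would in any case raise PainSim- ratings and work against hypothesis 1.

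**Conclusion.** The point holds as an inexpensive improvement, not as an error in the planned test. The trial randomises order and then does not use it in the models that it names. For assumed period effects of 0.25 or 0.50 SD, at dz = .40 and two-sided alpha .05, power at N = 51 is about 78% or 71% without order and about 80% with it. At N = 56 it is about 82% or 75-77%, against 83-84%. If there is no period effect, including order costs at most about a percentage point. These figures are for a single paired outcome, as in the plan's own sample-size calculation; power for the multivariate tests was not computed.

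The resting rating is of low priority. Its value is a lab-day baseline and a descriptive check of resolution in those with PainSim+ first, not a usable carryover test.

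**What to change.** 1. **Order in the models.** Before phase 2 is analysed, state that the condition models include order as a between-subjects factor and its interaction with condition, with the two orders weighted equally in the condition effect. Keep all participants. Do not use a carryover test to choose the analysis set, for example by falling back on the first condition alone. Cost: one error degree of freedom and no new data.

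2. **Optional resting rating.** In phase 2, add one low-back-pain VAS at rest with the simulator off before each condition, placed after the stress questionnaire so that it does not influence that score. The article does not say when the simulator is put on; this placement assumes it is after the questionnaire. Report the second rating descriptively in those with PainSim+ first. It will also contain soreness from the tasks, since "In the lifting task, an additional specification is to put a time limit of one minute". An end-of-session rating is not proposed: Stress (phase 2) takes saliva "directly after the two sets of movements tasks (s2), and 15 min after s2 (s3"), whereas Lab appointment ties s2 to the first set and s3 to the second, so such a rating would have no firm time. Cost: two single items per session and the possible priming of the fear ratings. If the team judges that risk too high, item 1 stands on its own.

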#### Fear of movement (phase 2).

Participants will rate how fearful they assess each impending movement task following its explanation but prior to its execution using a VAS scale (0 = *no fear*; 10 = *extreme fear*), resulting in 12 ratings.

#### Mobility (phase 2).

We will examine mobility by the motion capture technologies (Xsens and EmpkinS technology) and compute a set of movement features based on data from both motion capture modalities separately to compute the effect of the back pain simulator. These features are intended to characterize changes of lumbar range of motion (LROM), lumbar flexion (LF), and movement velocity (MV), among others. LF refers to the angle between the sacrum (S1/ S2) and lumbar-thoracic (L1/ T12) vertebrae. LROM refers to LF and extension, lateral bending and rotation between the above-mentioned vertebrae (S4 Fig). MV will be defined as the time participants need to execute a movement task, such as achieving maximum bending in the lifting and pick-up test.

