Irrespective of how FA beliefs arise, they can have wide-ranging consequences across physical, psychological, social, and societal domains [21]. On a physical level, continued inactivity may lead to deconditioning, increased pain sensitivity, and further functional decline, potentially resulting in a vicious cycle of disability [22,23]. Psychologically, FA is associated with feelings of helplessness [24], depressive symptoms [11,23], and general mental distress [23]. It has also been linked to poorer psychological and functional treatment outcomes in chronic pain patients [23]. Socially, FA can lead to disengagement from both professional and private life [21], leading to a reduced quality of life. These effects translate into both direct costs due to higher healthcare utilization and prolonged treatment and indirect costs, such as increased sick leave and work loss [25].

If avoidance of a movement is not possible, many CPLBP patients with FA exhibit guarded movements, such as stiffening to protect the spine [26,27]. These protective movements have been examined using surface electromyography (sEMGt), sensor-based motion capture systems, and psychometric assessments.

SEMGt studies have analyzed trunk muscle activity during gait tasks, with mixed results in relation to FA behavior [28,29]. Ghamkhar and Kahlee [29] reported increased activity in muscles associated with back pain, whereas Pakzad et al. [30] found no significant change in overall muscle activation levels, but observed altered variability in muscle activation patterns. Some studies employed sensor-based motion capture systems to assess FA-related movement patterns during potentially threatening movement tasks, both in persons with CPLBP [27] and pain-free individuals [26]. Matheve et al. [27] identified a reduced lumbar range of motion while Knechtle et al. [26] observed decreased lumbar flexion during tasks rated as potentially harmful. Most of these studies focus only on certain muscle groups, a single movement or mobility parameter, resulting in a lack of a standardized, integrated paradigm.

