Phase 2 will examine differences between participants with and without experimentally induced lower back pain in back-pain-related movement parameters during standardized movement tasks and investigate the related stress responses. In addition, we will collect self-report data on FA and investigate whether FA moderates the movement parameters and stress responses in the pain condition.

The following hypotheses will be tested:

(1) The task-related ratings of pain intensity are higher in the condition with the back pain simulator (PainSim+) than without (PainSim-).(2) The fear of movement ratings are higher in the condition with the low back pain simulator (PainSim+) than without (PainSim-).(3a) The task-related ratings of motion impairment are higher in the condition with the back pain simulator (PainSim+) than without (PainSim-).(3b) The mobility (measured through lumbar range of motion (LROM), lumbar flexion (LF), and movement velocity (MV)) is lower in the condition with the low back pain simulator (PainSim+) than without (PainSim-).(3c) Observer ratings of performance of task execution are worse in the condition with the low back pain simulator (PainSim+) than without (PainSim-).(4a) The task-related ratings of emotional distress are higher in the condition with the low back pain simulator (PainSim+) than without (PainSim-).(4b) The subjective stress ratings is higher in the condition with the low back pain simulator (PainSim+) than without (PainSim-).(4c) The heart rate variability (HRV) is lower in the condition with the low back pain simulator (PainSim+) than without (PainSim-).

In exploratory analyses, we will examine whether even in this analogue sample self-reported FA is associated negatively with mobility and HRV, and positively with subjective stress reports, salivary stress markers (alpha-amylase, cortisol), and pain ratings.

This integrated design allows for the combined assessment of physiological stress responses, behavioral changes, and movement-related aspects across standardized back-stressing movements.

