#### Back pain simulation.

To induce lower back pain, a back pain simulator from Produkt + Projekt Wolfgang Moll (Niederstotzingen, Germany) is employed [68]. The back pain simulator is a standalone component of an age simulation suit, the GERonTologic simulator (GERT). It consists of a black vest resembling a motorcycle back protector (see S3 Fig), that uses six large spike rivets (three on each side next to the spine) to simulate mechanical “stabbing” pain in the lower back. The vest is secured with two shoulder straps and a Velcro waist belt that allows adjustment of its tightness, and, consequently, pain intensity. To our knowledge, this back pain simulator is the only mechanical device designed to replicate lower back pain. Initial results indicate that wearing the age simulation suit leads to a decrease in functional and physical performance of young and older adults across various tasks requiring both gross and fine motor skills [69,70]. A preliminary test with the back pain simulator on a small sample revealed similar behavioral adaptations during the BPS movement tasks. Participants tended to stiffen and straighten their backs while moving and often bent the knees rather than their backs to pick up objects.

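### Movement velocity is defined as a duration, which contradicts the direction of hypothesis 3b, and time to maximum bending mixes speed with amplitude

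*Protocol article*

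**What the plan says.** Hypothesis 3b (Introduction) reads: "The mobility (measured through lumbar range of motion (LROM), lumbar flexion (LF), and movement velocity (MV)) is lower in the condition" with the simulator than without it. The exploratory statement that follows the hypotheses expects that "self-reported FA is associated negatively with mobility and HRV".

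The outcome section on mobility (phase 2) defines the third indicator: "MV will be defined as the time participants need to execute a movement task", with the example "such as achieving maximum bending in the lifting and pick-up test".

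Statistical methods enters LROM, LF and MV together in the second MANOVA, or in separate ANOVAs if the correlations among the variables point that way. The article nowhere says that MV is inverted, reverse-scored or related to the amplitude of the movement.

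**The concern.** A velocity and a duration run in opposite directions. If pain slows a participant over a given movement, the quantity defined as MV goes up, whereas 3b places MV among indicators that should go down. The exploratory prediction for fear avoidance flips for MV in the same way. The article does not leave the definition open. It gives one, and that definition does not fit its own hypothesis.

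There is a second problem that a sign change does not remove. In the article's own example the timed movement ends at the participant's maximum bend. How far that bend goes is itself expected to change: 3b predicts lower LROM and LF, the Introduction cites a study in back pain patients that "identified a reduced lumbar range of motion", and in the small preliminary test of the simulator participants "often bent the knees rather than their backs to pick up objects". A shorter movement takes less time at the same speed.

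At stake is whether one of the three mobility indicators can be read as support for 3b or against it. If the direction is settled only after the data are seen, either result could be presented as support.

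**Working it through.** **1. The plan's own figure, to see which test is planned.** Inputs from the sample size section: d = .40, alpha = .05, power = .80, N = 51; sidedness is not stated. A paired t test (noncentral t) gives:

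- two-sided: N = 52 (power 0.808), with power 0.7999 at N = 51;
- one-sided: N = 41.

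The stated 51 therefore matches a two-sided calculation to within one participant and does not match a one-sided one. This agrees with the F tests in Statistical methods. The sample size does not depend on how MV is defined.

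**2. Direction.** Let T be the time to complete a movement, A the amplitude covered and v the mean speed, so T = A / v. At equal amplitude, a speed 20% lower (assumed) gives T ratio = 1.00/0.80 = 1.25. MV as defined rises by 25%, while 3b read literally calls for a fall.

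**3. Effect of the sign on the planned test.** For the vector of within-person differences with mean m and covariance S, Hotelling T² = n m′S⁻¹m. Reversing the sign of MV replaces m by Dm and S by DSD, with D = diag(1, 1, −1). Then n(Dm)′(DSD)⁻¹(Dm) = n m′S⁻¹m, so nothing changes. One simulated data set of 51 participants gave 30.55 both before and after the reversal. A univariate repeated-measures F with two conditions equals t², which also ignores the sign.

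**4. Amplitude.** The documents give no expected percentages, so the changes below are assumptions for illustration. Ratios are simulator condition over control.

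| Speed | Amplitude | Time = amplitude/speed | MV as written, against 3b | MV with sign reversed |
|---|---|---|---|---|
| 0.80 | 1.00 | 1.25 | higher: contradicts | reads as slower (correct) |
| 0.80 | 0.80 | 1.00 | no change | slowing not visible |
| 0.90 | 0.80 | 0.89 | lower: agrees, for the wrong reason | reads as faster (wrong) |
| 1.00 | 0.80 | 0.80 | lower: agrees, without any slowing | reads as faster (wrong) |

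The time ratio runs from 0.80 to 1.25, and the two extremes are not ordered by speed: the longest time and an unchanged time both come from a 20% slowing. Using 1/T corrects the direction but leaves A in the measure.

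**The case against.** The strongest reply is that the grammatical subject of 3b is mobility, with MV only listed as an indicator. A longer time plainly indicates less mobility, so the authors very probably mean slower movement. That is a fair account of intent. It does not repair the text: the indicator is named a velocity, defined as a time and entered under that name, with no statement of direction.

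Three stronger readings are tempting, and the document does not support them.

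- **Loss of power.** A reader might infer that 3b has almost no chance of being confirmed. A one-sided test in the literal direction, with a true slowing of d = .40 in time and N = 51, would have power of about 0.000004, against about 0.88 in the other direction. No one-sided test is planned. The planned F tests would detect the slowing as well under either sign.
- **Lifting time fixed by design.** The lifting task instructs the team to "put a time limit of one minute and count the repetitions of the participant", so one might conclude that its duration is constant. The article's own example for lifting is time to maximum bending, a time within the movement and not the one-minute block. What remains is that the timed interval should be stated for each task.
- **Confounding in every task.** Where the chair or an object largely sets the path, as in sit-to-stand, the dependence on amplitude is weaker. Bending the knees instead of the back also means that less lumbar bending need not shorten the whole task.

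It is also true that LROM and LF stand beside MV in the same MANOVA, so amplitude is analysed. That helps a careful reader, but it does not turn a time into a measure of speed.

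**Conclusion.** The concern holds in a limited form. The definition of MV conflicts with the direction of 3b and of the exploratory fear-avoidance prediction. The consequence lies in the stated hypothesis, the univariate follow-up and the interpretation. It does not lie in the omnibus p-value, the power or the sample size.

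For time to maximum bending there is a further validity problem: a real slowing can be hidden or reversed by the fall in amplitude that 3b itself expects. The identity T = A / v is exact when amplitude and mean speed refer to the same segment and the same endpoint. The size of the effect is unknown, because the percentages used above are assumed. The problem is weaker for tasks with a fixed path.

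**What to change.** Choose one of two definitions before phase 2 data are analysed, and use it in the hypotheses, the outcome section and the analysis alike.

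- **Preferred:** define MV as mean or peak lumbar or trunk angular velocity over a stated movement phase (for example, from movement onset to maximum bend). Hypothesis 3b and the exploratory prediction can then stand as worded. The motion capture section says that the suit records angular velocity and yields joint angles, so the data will be available.
- **If a time is kept:** call it movement time and state the timed interval for each task. Predict it to be higher with the simulator and positively associated with fear avoidance. Interpret it together with the amplitude covered, or normalise it by that amplitude.

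The cost is one revised definition and a little extra feature computation. No additional measurement or participants are needed.
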